#### Secondary outcomes

Difference between the two study groups at 8 weeks post-baseline in:
Mean change in conformity to masculine norms as measured by the Conformity to Masculine Norms Inventory (CMNI-22) [25].Mean change in depression risk as measured by the Male Depression Risk Scale Short Form [26].Mean change in perceived social support as measured by the Modified Medical Outcomes Study Social Support Survey (MOS-SS) Emotional/Informational support subscale [27]Mean change in quality of life as measured by the Child Health Utility Instrument (CHU-9D) [28]

#### Economic outcomes

The economic outcome of the intervention will be determined in comparison to the waitlist control group from a health care perspective and a partial societal perspective. The CHU-9D data will also enable the calculation of quality-adjusted life years (QALYs) that will be used in a cost-utility analysis. Key costs and their measure(s) include (i) intervention costs, (ii) parents’ productivity losses (based on the number of days their son is absent from school), and (iii) health care service costs during the trial follow-up period (collected using a modified Resource Utilization Questionnaire (RUQ) [29]).

### Participant timeline {13}

The participant timeline is shown in Fig. 1.

**Fig. 1 Fig1:**
[figure not shown]
Schedule of enrolment, interventions, and assessments

From the end of 2020 and throughout 2021 and 2022, as schools contact *Tomorrow Man* to book in workshops for the following year, *Tomorrow Man* will undertake a school eligibility check with interested schools (i.e., to ensure it meets the trial inclusion criteria). Contact details of eligible schools will be forwarded to the researchers who will provide schools with information about the trial and ask school principals to give their consent for the schools to take part. The researchers will randomize the school to the intervention or waitlist group.

All schools will then be sent a Plain Language Statement and parental consent form for all parents of eligible students. Schools will distribute this information to parents, who will be asked to provide consent for their son’s participation. Students whose parents have consented will receive an email informing them that their parents have consented to their participation in the trial and that shortly they too will receive further information. This email will allow checks for “bounce-backs” and confirm any email errors with parents prior to student participation.

For schools in the intervention group, soon after randomization, schools will schedule a class time for all the male students who are enrolled to take part in the workshop. This class time will be within the 2 weeks prior to the workshop. The school will advise the researchers of this class time and the researchers will direct Logicly to send a second email to students with parental consent. The email will contain a link to the Plain Language Statement, assent form, and baseline questionnaire. The school staff member will activate the baseline questionnaire within the class time using a link provided to them by Logicly. After reading the Plain Language Statement and providing their assent, the students will have access to complete the online survey which will take about 20 min. Intervention group schools will then receive the workshop within the following 2 weeks. Schools will be asked to schedule a second-class time with students 4 to 6 weeks after students received the workshop to administer the follow-up questionnaire. Prior to this class, students who completed the baseline questionnaire will receive an email containing a link to the deactivated online follow-up questionnaire. Within the class time, a staff member will direct students to the email, if they have received it. The staff member will activate the follow-up questionnaire and the students will complete it

For schools in the waitlist group, soon after randomization, the schools will schedule a class time for all the male students who are enrolled to take part in the workshop. The school will advise the researchers of this class time and the researchers will direct Logicly to send an email to students with parental consent containing a link to the Plain Language Statement, assent form, and baseline questionnaire. The school staff member will activate the baseline questionnaire within the class time using a link provided to them by Logicly. After reading the Plain Language Statement and providing their assent, the students will have access to complete the online survey which will take about 20 min. The schools will then provide school as usual for the students over the following weeks. Schools will be asked to schedule a second class time for students to complete the follow-up questionnaire 6 to 8 weeks after the baseline questionnaire. The staff member will activate the questionnaire and the students will complete it. They will receive the workshop after the second survey has been completed by the students.

In either group, if a student has completed the baseline questionnaire, but cannot locate the email for the follow-up questionnaire, then an automated process will enable the teacher to provide the student email to Logicly who will resend the email.

If schools or individual participants withdraw from the trial at any time (prior to baseline or follow-up questionnaire assessment), the data provided by participants up to that point will be included in the trial.

### Sample size {14}

For 90% power and a two-sided 5% significance level, a sample of 1000 participants across 40 schools (a minimum of 25 students on average per school) will be required to detect a standardized effect size of 0.3 in mean change in GHSQ score between the study groups. This is equivalent to a 3-point difference in mean GHSQ score between the study groups (standard deviation of 10), which was found in the recent Man Up trial with adult men [30]. Sample size accounts for the correlation of outcomes within schools of 0.03 [31] and assumes 20% attrition at follow-up of students and allows for the potential loss of two schools over the period of the study.

### Recruitment {15}

Five school terms (terms 2, 3, and 4 in 2021 and terms 2, 3, and 4 in 2022) have been provided for data collection from the students. The desired sample size of 1000 participants across 40 schools is feasible within *Tomorrow Man*’s forecast of approximately 5000 male student participants in 150 workshops across Australia in the study period.

## Assignment of interventions: allocation

### Sequence generation {16a}

Schools will be randomized in a 1:1 ratio to the intervention or control group using an allocation sequence stratified by location of the schools (rural or urban), state (Victoria, NSW, or WA), and mode of workshop delivery (face-to-face or online), generated using a biased-coin algorithm [32]. The imbalance tolerance for the biased-coin algorithm will not be disclosed until all the schools have been randomized to ensure concealment.

### Concealment mechanism {16b}

*Tomorrow Man* will invite schools to the trial and then will pass the details of interested schools onto one of the researchers. This researcher will obtain school consent and will collect details including school location, state, and mode of workshop delivery. The researcher will then pass this deidentified information to the trial statistician who will randomly allocate each school to either the intervention or the waitlist group. The statistician will advise the researcher of the allocation who will then re-identify the school. The rest of the research team, including the statistician, will remain blinded to the identity of schools until data analysis is complete. *Tomorrow Man* workshop facilitators will be delivering workshops throughout the year to schools that are participating in the trial, as well as to schools that are not participating. *Tomorrow Man* will not tell facilitators which schools are participating. Parents and students in schools in each group will not be aware of the presence of the alternative group and will not be informed that their participation is to evaluate the *Breaking the Man Code* workshops. They will be told that the study is about male student wellbeing.

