### Intervention description {11a}

The intervention group will receive the *Breaking the Man Code* workshop. This workshop will be delivered in class time at school by a *Tomorrow Man* trained facilitator. The workshops are delivered over 2 h in a face-to-face or an online format (i.e., via a video meeting platform) to groups of 30–35 male students. Prior to the COVID-19 pandemic, workshops were delivered face-to-face only. In response to the pandemic, and associated lockdowns and travel restrictions, the online mode was developed in 2020 during the design phase of the trial. The workshop content is similar in both delivery modes, with small adjustments. The mode of delivering is now generally chosen based on school preference, facilitator availability (particularly when the facilitator is required to travel to rural areas), and, where relevant, COVID restrictions. One facilitator usually provides all the workshops within one school, with up to six facilitators delivering the workshops across schools nationally. The average number of workshops per school is three, with an average of 33 students per workshop.

The interactive *Breaking the Man Code* workshops facilitate honest and authentic conversations with year 10, 11, and 12 male students, in order to define a masculinity that “generates purpose, pride, and health for the men of today and tomorrow.” The workshops aim to develop protective factors such as positive attitudes towards help-seeking, emotional expressiveness, and social support. The workshop involves discussion about the stereotypes of what it means to be a man in Australia today, and the impacts that these can have on men’s mental health. It explores the (unwritten) rules that exist for men on how to behave (the “man code”) and investigates why men and boys feel obliged to live up to these expectations and stereotypes. The workshop then unpacks the impact of the “man code” on boys and men and allows boys to share their experience living with the stereotypes while encouraging them to question norms and redefine their own rules.

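### The researcher who seeks school consent is also told every allocation, so concealment under the biased coin is incomplete, though not absent

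*Protocol article*

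**What the plan says.** Concealment mechanism {16b} sets out the chain. The workshop provider "will invite schools to the trial and then will pass the details of interested schools onto one of the researchers". Of that researcher it says: "This researcher will obtain school consent and will collect details including school location, state, and mode of workshop delivery". The next step is separate: "The researcher will then pass this deidentified information to the trial statistician who will randomly allocate each school". The result then goes back to the recruiter: "The statistician will advise the researcher of the allocation who will then re-identify the school".

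Sequence generation {16a} describes a 1:1 sequence "generated using a biased-coin algorithm", stratified by location (2 levels), state (3) and delivery mode (2). It names one safeguard against prediction: "The imbalance tolerance for the biased-coin algorithm will not be disclosed until all the schools have been randomized to ensure concealment".

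Three other sections bear on the point. Participant timeline {13} has schools entering from the end of 2020 and throughout 2021 and 2022, as they book workshops. Study setting {9} says that every school in the three states that receives a workshop in the trial period will be invited. On the third stratification factor, Intervention description {11a} says: "The mode of delivering is now generally chosen based on school preference, facilitator availability" and, where relevant, COVID restrictions.

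**The concern.** A biased coin corrects imbalance by favouring the arm that is behind. Anyone who holds the allocation history with the strata can see which arm that is. Here this person is the one who obtains the next school's consent and submits its details. Deidentifying the details keeps school identity from the statistician. It does not keep the likely arm from the recruiter.

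Withholding the tolerance hides when the coin begins to lean. It does not hide which way it will lean once it does. A recruiter who expects a particular arm could, without intending to, pursue a school more or less actively or submit one school before another. That would be selection at the level of the randomised unit, in a trial with about 40 such units.

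**Working it through.** **The plan's own figures.** The article gives no figure for predictability. Its sample size supplies the inputs and reproduces. A 3-point difference, SD 10, two-sided 5% and 90% power need 234 per arm. With 25 × 0.8 = 20 completers per school and ICC 0.03, the design effect is 1 + 19 × 0.03 = 1.57. The total is 2 × 234 × 1.57 = 735 completers, or 735/20 = 36.7 schools. That rounds to 38 for equal arms, and 2 lost schools make 40 schools and 1000 students.

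**Predictability.** There are 2 × 3 × 2 = 12 cells and 40/12 = 3.3 schools per cell on average. The coin probability, the tolerance and the level of balancing are not given, so all rules below are assumed. Each was simulated 2000–3000 times with 40 schools. The guesser knows all earlier allocations and names the lagging arm.

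| Assumed rule | Correct guesses, equal cells | Correct guesses, uneven cells |
|---|---|---|
| Efron coin 2/3, within cell | 58.8% | 59.3% |
| Efron coin 0.8, within cell | 64.5% | 65.0% |
| Fair until imbalance 1, then forced | 71.2% | 71.5% |
| Fair until imbalance 2, then forced | 57.1% | 58.0% |
| Fair until imbalance 3, then forced | 52.3% | 53.6% |
| Fair until imbalance 2, then 0.7 | 53.5% | 54.5% |
| Fair until imbalance 2, then 0.8 | 54.9% | 56.0% |
| Fair until imbalance 3, then 0.8 | 51.5% | 52.6% |
| Efron coin 2/3, on margins | 64.5% | 64.5% |
| Efron coin 0.8, on margins | 75.0% | 75.0% |

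The uneven mix is assumed: location 30/70, states 55/30/15, mode 75/25.

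Two hand checks agree with the table:
- Efron 2/3, equal cells: 47.4% of schools meet a tied cell, so the rate is 0.474 × 0.5 + 0.526 × 2/3 = 0.588.
- Forced at imbalance 1, equal cells: every second school in a cell is certain. That is about (3.33 − 0.5)/2 = 1.42 per cell, or 17 of 40 (42.5%), so the rate is 0.5 + 0.425/2 = 0.71.

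Always naming the lagging arm needs no knowledge of the tolerance. Inside the tolerance the coin is fair and the guess costs nothing; beyond it the coin leans the way guessed. Withholding the tolerance hides which guesses are dependable, but leaves the overall rate unchanged.

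**Do the strata drive this?** No. Without stratification the rates are higher: 62.1% for Efron 2/3 (58.8% with 12 cells), 61.9% for forced at 2 (57.1%) and 57.8% for forced at 3 (52.3%). More cells mean more ties.

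**Upper bound on bias.** Let g be the correct-guess rate. Assume that every guess is acted on, by steering schools half a between-school SD above or below average: δ = 0.5 × √0.03 × 10 = 0.87. The bias is 2δ(2g − 1).
- g = 0.515: 2 × 0.87 × 0.03 = 0.05 points (2% of 3).
- g = 0.712: 2 × 0.87 × 0.424 = 0.73 points (about 24% of 3).
- g = 0.75 (margins only): 2 × 0.87 × 0.5 = 0.87 points.

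The standard error is 10 × √(2 × 1.57/380) = 0.91. The false-positive rate then runs from essentially 5% at 0.05 points to about 13% at 0.73 points. All of this is before baseline adjustment.

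**The case against.** The other side has a strong case on size and on several inferences.

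- **Concealment might be said to fail altogether.** The text does not support that. A separate person allocates each school, after consent, and the tolerance is withheld. The guess is probabilistic unless a forcing rule has reached its limit, and the article does not say that a forcing rule is used.
- **A biased coin might be said always to lean.** A coin with a tolerance may be fair until the tolerance is reached. That reading puts the floor of the range near 52%.
- **Small strata might be blamed.** With within-stratum balancing they lower predictability, as shown in the working.
- **The provider might be thought to know earlier allocations,** because workshop timing depends on them. The article does not say so, and the point does not rest on it.
- **The route to selection is narrow.** Schools request the workshop themselves and, under Eligibility criteria {10}, agree in advance to either period. All eligible schools are to be invited, and nothing lets the recruiter set the delivery mode. No section gives the recruiter help-seeking data before baseline. The primary model in {20a} adjusts for baseline GHSQ and the stratification factors.
- **A condensed article may leave submission order to the full protocol.** Agreed, so that silence is not counted as a fault.

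These objections limit the size. They do not remove the core. The article itself gives both roles to one person and offers a safeguard that does not prevent prediction from the history.

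**Conclusion.** The concern holds in limited form. Concealment is incomplete because the person seeking school consent also receives the running allocations, and withholding the tolerance does not stop better-than-chance guessing.

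The extent depends on features that the article does not state. Under the assumed rules the gain over 50% runs from about 2 to 21 percentage points with within-stratum balancing, and reaches about 25 in one marginal variant.

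The bias itself cannot be determined from the document. A reader might take the upper end of the calculation as a forecast. It is not one: it assumes a rule forced at an imbalance of 1, every guess acted on, an ability to tell better from worse schools, and no baseline adjustment. The likely effect is much smaller. The case for change is that a known route to bias can be narrowed at almost no cost.

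**What to change.** Amend {16b} for schools not yet allocated:

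1. Submit and allocate schools strictly in order of time-stamped principal consent, or in batches, with location, state and intended delivery mode locked at that time. This removes discretion over order and over the recorded stratum.
2. Where the existing team allows, release each allocation to a team member who does not seek school consent. That person should also handle the scheduling that follows, because the timing of the questionnaires relative to the workshop reveals the arm. This step addresses what the first cannot: how actively a school is pursued before it consents.

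The cost is protocol wording and a reassignment of tasks. No extra data, schools or analysis are needed. The downside is that one more team member knows school allocations, which {16b} and {17a} would have to acknowledge, or a short wait if batches are used.

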### Implementation {16c}

Online questionnaire data collection will be undertaken by Logicly (the data management subcontractor) who will use a purpose-built online platform for the survey. They will generate unique URLs for each participant based on their email address, so that participant responses can be connected across the two questionnaires. At the end of the trial, Logicly will provide the questionnaire data to the researchers in a deidentified, blinded format. Unblinding of the groups will occur after data analysis.

## Assignment of interventions: blinding

### Who will be blinded {17a}

The students participating in the trial, the workshop facilitators, the statistician, and the researchers not involved in randomization will be blinded to the names and allocation of schools. Schools will know their allocation based on the timing of the workshop relative to the questionnaires but will be asked not to inform students or workshop facilitators. *Tomorrow Man* workshop facilitators will be blinded, as they will not know which schools are participating in the trial.

### Procedure for unblinding if needed {17b}

If a school or participant withdraws from the trial, unblinding will be required to ensure that participants are not contacted for the next stage of the trial (e.g., the baseline or follow-up questionnaire). Schools will advise the researchers who will then advise Logicly. Participants can notify the researchers via the trial email address (that is monitored by the researcher who was involved in randomization) provided on the Plain Language Statement. The researchers will seek to determine the reason for school or participant withdrawal.

## Data collection and management

### Plans for assessment and collection of outcomes {18a}

Outcome measures will be collected from students at baseline after randomization of schools. For the intervention group, data will be collected at baseline within 2 weeks of the intervention being delivered. The follow-up questionnaire will be administered 4–6 weeks after the workshop. For the waitlist control group, baseline and follow-up data collection will occur 6–8 weeks apart before the workshop is delivered.

For both groups, the baseline and follow-up questionnaires will be administered online within an allocated class time. The baseline questionnaire will include demographic questions and the measures related to the primary, secondary, and economic outcomes that are described below. The follow-up questionnaire will be a repeat of the baseline questionnaire, minus the demographic questions, with the addition of some open-ended questions for the intervention group.

#### Demographic information

Five demographic questions will be asked: age (in years); gender (male, transgender male, non-binary/gender diverse, don’t know, prefer not to say, or participant described); sexual orientation (gay or homosexual, straight or heterosexual, bisexual, something else, do not know, prefer not to say); language mainly spoken at home (English, Italian, Greek, Cantonese, Arabic, Mandarin, Vietnamese, other (specify)); and Aboriginal or Torres Strait Islander status (No, Aboriginal, Torres Strait Islander, both).

#### Primary outcome

Intentions to seek help for a personal or emotional problem will be measured by the General Help-seeking Questionnaire (GHSQ) [24]. The GHSQ has been found to be reliable and valid and to be a suitable measure of help-seeking intentions in a range of contexts, and the scale can be modified to add extra response items. The GHSQ asks participants: “If you were having a personal or emotional problem, how likely is it that you would seek help from the following people or services?” Response options include an intimate partner, friend, or doctor. Participants respond on a 7-point Likert scale (1 = extremely unlikely to 7 = extremely likely). The following additional response options will be included: online health chat rooms, online searches for health information, social media, and someone at school. The final score is the sum of responses to the 10 items (range 10–70), where higher scores indicate higher intentions to seek help.

Perceived social support will be assessed using the emotional/informational subscale of the Medical Outcomes Study Social Support Survey (MOS-SS) [27]. This 8-item subscale asks participants about the kind of emotional and informational support available to them, such as someone: to turn to for suggestions about how to deal with a personal problem, who understands your problems, and to give you good advice about a crisis. The items are answered using a 5-point Likert scale (1 = none of the time to 5 = all of the time). The sum of the item scores provides a total score ranging between 8 and 40 where higher scores reflect higher levels of perceived support. The scale has been found to have good psychometric properties among young non-clinical populations [37].

Quality of life will be assessed using the Child Health Utility Instrument (CHU-9D) [38]. This 9-item scale asks participants about their functioning today across domains of worry, sadness, pain, tiredness, annoyance, school, sleep, daily routine, and activities. The items are answered using a 5-point Likert scale (1 = I do not feel X today to 5 = I feel very X today). The CHU9D has been recommended for measuring the quality of life in adolescent populations in Australia [39].

